### Blinding

Both participants and outcome assessors are blinded to the treatment arm during the entire study period. By definition, surgeons performing the operation cannot be blinded. To avoid bias, operating surgeons will not be involved in outcome data collection and will be instructed not to reveal the group allocation to researchers or the patients themselves. In addition, they will be instructed not to specify the closure method in the operative records, instead documenting that the fascia was closed according to the TROCAR trial protocol. All other intraoperative and postoperative details will be recorded as usual. Access to data on REDCap will be limited based on blinded, unblinded and administrator roles.

An emergency unblinding process will be available at all hours of the day. Consultant surgeons are permitted to request an emergency unblinding following direct discussion with the Principal Investigator. Unblinding rates will be logged and checked throughout the trial by the research team and Data Monitoring Committee.

### Protocol deviations

Major protocol deviations are defined as those which become necessary to protect participant safety or failure to report a serious adverse event to the Research Ethics Committee (REC) within 14 days. The decision to withhold Duramesh in an intervention group patient or the placement of Duramesh in a control group patient for safety reasons are classified as major protocol deviations. Minor protocol deviations can be managed internally and include out-of-window visits, accidental unblinding and administrative errors. Accidental unblinding will be managed using a different blinded sonographer for outcome assessment. Non-compliance with the allocated treatment arm due to surgeon error is considered an administrative error. Protocol deviations will be documented, and an intention-to-treat analysis will be performed, with major deviations excluded from the per-protocol set. Major deviations are reported to the REC and minor deviations are reported to the Trial Steering and Data Monitoring and Safety Committees.

In the event of a return to theatre deemed unrelated to the method of closure (e.g. complication from intraabdominal compartment), the patient will be re-closed according to the study arm to which they were initially allocated to. For device-related reoperation, the explant of Duramesh can be undertaken if felt to be clinically indicated, and the foreign material will be sent to the laboratory for microbiological and/or histological analysis. After the explant, the fascia will be closed by a method up to the discretion of the operating surgeon.

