### Sample size

This study will be powered for detecting a difference in the primary outcome between groups. Previous prospective studies with similar follow-up duration record an incidence of trocar-site hernia in the region of 25% [7–9]. An absolute reduction in primary outcome of 15% is expected within the intervention group, down to an occurrence of 10%. The best available evidence comes from a systematic review of Duramesh implantation for laparotomy and ventral hernia repair with a median incisional hernia rate of 3.4% after 1 year [13]. An occurrence of 10% was selected as a conservative estimate of the effect size in the intervention group after 2 years. Therefore, using a significance level of 5% and power of 80%, it is calculated that 100 patients per group, 200 in total, are required. After factoring in a 20% rate of loss to follow-up, a total of 250 participants will be included in the trial.

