### Statistical methods

Results will be reported in accordance with the CONSORT guidelines for randomised controlled trials [21]. Analyses will be on an intention-to-treat (ITT) basis and will be conducted according to a pre-specified statistical analysis plan. The primary analyses will use data from all participants randomised who provided written informed consent, whose data is suitable (i.e. not missing). Any missing data will be reported, and data will be summarised as observed without imputation. Missing data values will be omitted from the primary analyses.

Continuous demographic variables such as age and BMI will be summated by the mean ± standard deviation if found to be normally distributed, and median with range or inter-quartile range otherwise. Categorical variables will be summarised by the number and percentage in each category.

To allow for differences in outcomes between participating surgeons, all analysis will be performed using generalised mixed (multilevel) models. Study group will be included as a fixed effect, with surgeon as a random effect. The primary outcome, the occurrence of trocar-site hernia over 2 years, will be analysed using a model assuming a binomial distribution with an identity link function. This will enable the percentage difference in outcome between groups to be calculated, which will be presented with a corresponding confidence interval. Secondary outcomes measured on a binary scale will be analysed using an equivalent approach to the primary outcome. Length of stay in hospital will be analysed using a linear mixed model. This outcome is expected to follow a positively skewed distribution and will thus be given a log transformation before analysis. All tests will be two-sided and a *p* value < 0.05 will be considered as statistically significant. Confidence intervals will be calculated at the 95% level.

A sensitivity analysis will be performed for the primary outcome. This will use multiple imputation for patients with missing outcome data. This will be performed using chained equations.

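### The per-protocol set keeps participants closed with the wrong material through surgeon error and drops correctly closed participants whose SAE was reported late, so it does not hold those treated as allocated

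*Protocol article*

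**What the plan says.** All the relevant rules are in one paragraph of the protocol article, under Protocol deviations.

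- **Major deviations** are those needed to protect participant safety, and also "failure to report a serious adverse event to the Research Ethics Committee (REC) within 14 days". A change of closure falls here when it is made for safety: withholding Duramesh in the intervention arm, or, in the other direction, "the placement of Duramesh in a control group patient for safety reasons are classified as major protocol deviations".
- **Minor deviations:** "Minor protocol deviations can be managed internally and include out-of-window visits, accidental unblinding and administrative errors".
- **Wrong closure by mistake:** "Non-compliance with the allocated treatment arm due to surgeon error is considered an administrative error".
- **Analysis sets:** "an intention-to-treat analysis will be performed, with major deviations excluded from the per-protocol set".

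The Statistical methods section makes intention-to-treat the basis of analysis: "Analyses will be on an intention-to-treat (ITT) basis and will be conducted according to a pre-specified statistical analysis plan". It gives no other definition of the per-protocol set.

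**The concern.** A per-protocol set should hold the participants who were treated as allocated. In this trial the closure material is the only planned difference between the arms (Standardisation), so receipt of the allocated material is the main adherence question. The rule as written does not ask it. It borrows a classification built for regulatory reporting and uses it to decide who is analysed.

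Two problems follow. Participants who did not receive their allocated closure can stay in, which pulls the two arms towards each other. Participants who did receive it can be removed because of how the site handled a report, and only if they had an SAE after randomisation. Membership then depends partly on a post-randomisation event, whose frequency could differ by arm, and on site reporting.

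The protocol itself foresees closure errors, since it assigns them a class. Twelve surgeons randomise and close (Setting). Allocation is made before the first incision, and the fascia is closed when the operation is complete (Randomisation, Standardisation).

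**Working it through.** **Step 1: apply the rules to four cases.**

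| Case | Closed as allocated? | Class | In per-protocol set? |
|---|---|---|---|
| Switch of closure for safety | No | Major | No |
| Same switch through surgeon error | No | Administrative, hence minor | Yes, under allocated arm |
| Closed as allocated, SAE reported to the REC after 14 days | Yes | Major | No |
| Closed as allocated, no deviation | Yes | None | Yes |

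The first and last rows are what one would want. The second and third are the wrong way round for a set meant to hold those treated as allocated.

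**Step 2: reproduce the plan's own figure.** Inputs from Sample size and Statistical methods: control risk 0.25, Duramesh risk 0.10, two-sided 5% significance, 80% power, 1:1 allocation. With mean risk 0.175:

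n = [1.960 × √(2 × 0.175 × 0.825) + 0.842 × √(0.25 × 0.75 + 0.10 × 0.90)]² / 0.15² ≈ 99.5, so 100 per arm.

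200 / (1 − 0.20) = 250. Both figures match the protocol, and the point raised here does not alter them.

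**Step 3: size of the retained error, as an illustration.** The documents give no rate of wrong closure, so the rate x is an assumption. It is also assumed that a wrongly closed participant carries the risk of the material received.

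Errors at rate x in both arms, kept as allocated:

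difference = [0.25(1 − x) + 0.10x] − [0.10(1 − x) + 0.25x] = 0.15(1 − 2x)

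Errors at rate x in the Duramesh arm only:

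difference = 0.25 − [0.10(1 − x) + 0.25x] = 0.15(1 − x)

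| Assumed error rate x | Both arms | Duramesh arm only |
|---|---|---|
| 0% | 15.0 points | 15.0 points |
| 2% | 14.4 points | 14.7 points |
| 5% | 13.5 points | 14.25 points |
| 10% | 12.0 points | 13.5 points |

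Excluding the wrongly closed participants returns the expected difference to 15 points under the same assumptions, with a slightly smaller set. At 5% that would be 0.05 × 100 = 5 participants per arm of the 100 evaluable.

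The effect of the late-report exclusion cannot be sized, because the documents give neither an SAE rate nor a rate of late reporting.

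**The case against.** The strongest reply is that little hangs on this set. TROCAR is a superiority trial analysed by intention to treat. The only sensitivity analysis that Statistical methods names for the primary outcome is multiple imputation. The per-protocol set appears once, in a subordinate clause, and no test or success criterion is attached to it. That stands, and it limits the severity.

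A second reply is that the statistical analysis plan, which is not shown, may define the set properly. It may, but the protocol is not silent here. It states a rule. An analysis plan that follows the rule inherits the fault, and one that departs from it contradicts the protocol.

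Third, error may be rare. Surgeons were trained, and the consultant who randomises also closes. Nothing in the documents supports any particular rate, so the figures above show only how the effect scales.

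Two stronger readings are tempting, and the documents support neither:

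- A reader might infer that the per-protocol set carries the same dilution as intention-to-treat and so corrects nothing. Safety-driven switches are classed as major and do leave the set, so it removes some crossover. The two would match on crossover only if no such switches occurred.
- A reader might infer that the late-report rule selectively removes the worst outcomes, including hernias. Under Adverse event reporting, trocar-site hernia and surgical site occurrences are not recorded as adverse events, so a hernia cannot itself trigger the exclusion. Any selection would be indirect, through participants with other serious events.

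**Conclusion.** The point holds for the per-protocol set as the protocol defines it. That set removes safety-driven crossover, keeps error-driven crossover under the allocated arm, and can remove participants closed as allocated because an SAE was reported late. It therefore does not hold those treated as allocated. It is not an as-treated set either, since nobody is regrouped by the closure received.

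Under the planning risks, each 1% of wrong closures kept in both arms takes 0.3 points off the expected per-protocol difference (0.15 points if errors occur only in the Duramesh arm). The loss is small at low error rates and 3 points at an assumed 10% in both arms. The classification fault does not depend on these rates.

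A reader might go on to infer that the primary result or the sample size is in doubt. Neither is: both rest on intention-to-treat, where participants are analysed as allocated by design. Severity is moderate or minor.

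**What to change.** Separate the two purposes that the paragraph now mixes.

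1. Leave the major and minor classes as they are for reporting. Moving surgeon error into the major class would also change its reporting route, since major deviations go to the REC and minor ones to the trial committees. The analysis does not need that.
2. Define the per-protocol set on its own terms: participants whose fascia was closed with the allocated material. Exclude anyone for whom this was not so, whatever the reason.
3. State that late reporting of an SAE to the REC is a regulatory deviation and not a ground for exclusion from the per-protocol set.

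The cost is the rewording of one protocol paragraph and a matching population definition in the analysis plan. No new data are needed, because deviations are already documented, and the 250 randomised are unchanged. Recruitment is expected to run to December 2026 with two years of follow-up after that, so the change can be made well before the final analysis. It should be fixed before outcomes are compared by arm.

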### Loss to follow-up

Our sample size calculations have factored in a 20% rate of loss to follow up, which is based on other studies in surgical populations requiring 2-year follow-up with imaging to detect incisional hernia [19, 20]. By consenting to participate, patients are consenting to the intervention, assessments, follow-up and data collection. Study participants are free to withdraw at any time.

Participants may be withdrawn from the trial by the research team if continued participation is no longer in their best interests. Reasons for discontinuing may include the following: intercurrent illness making data collection impossible, persistent non-compliance with protocol requirements hampering and/or biasing data collection, participant fulfils any of the intra-operative exclusion criteria, and participant loss to follow-up (e.g. moves abroad/not contactable).

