### Randomisation

Patients will be randomly allocated to either the intervention or control arm when they arrive in the anaesthetic room before knife to skin. The randomisation sequence was generated and is held by the trial statistician. Randomisation and assigning the intervention are performed by the operating consultant surgeon using a secure web-based system (sealedenvelope.com, Sealed Envelope Ltd., London, UK) ensuring allocation concealment. Following statistical advice, the computer-generated randomisation sequence (in 1:1 ratio) will use a block size of 4 and stratify according to BMI (≥ 30 or < 30) and diabetes (present or absent). The operating consultant surgeon will then close the trocar site with the material specified by the allocation arm.

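### The research team may withdraw randomised participants for persistent non-compliance, which can forfeit an obtainable 2-year scan and leave that outcome out of a primary analysis labelled intention-to-treat

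*Protocol article*

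**What the plan says.** Under Loss to follow-up, the protocol article states: "Participants may be withdrawn from the trial by the research team if continued participation is no longer in their best interests". The reasons it then lists include "persistent non-compliance with protocol requirements hampering and/or biasing data collection" and "participant fulfils any of the intra-operative exclusion criteria". Being lost to follow-up, for example because the participant cannot be contacted, is a separate reason in the same list.

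Under Randomisation, allocation takes place "when they arrive in the anaesthetic room before knife to skin". The intra-operative ground therefore acts after randomisation, and so does any later non-compliance.

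Under Statistical methods, "Analyses will be on an intention-to-treat (ITT) basis". The primary analyses use "all participants randomised who provided written informed consent, whose data is suitable (i.e. not missing"), and "Missing data values will be omitted from the primary analyses". Multiple imputation by chained equations is a sensitivity analysis for the primary outcome.

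The primary outcome is the cumulative occurrence of trocar-site hernia over 2 years, defined by ultrasound. Scans are scheduled at 3 months, 1 year and 2 years.

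**The concern.** In a trial of continuing treatment, a non-compliance clause might concern whether treatment goes on. Here the treatment is a single act, finished before the participant wakes. What remains for the participant to comply with is data collection, so the clause gives the team the power to stop seeking data from someone whose attendance has been poor.

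A participant who misses the 3-month and 1-year visits may still come at 2 years. Withdrawal from the trial may turn that partial loss into a complete one. The limb about biasing data collection is the more troubling, because it invites a judgement after randomisation about whose data should continue to be sought.

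Two things are at stake. If withdrawal is related to hernia risk and differs between arms, omitting those outcomes biases the risk difference. If it is unrelated to outcome, it costs only precision and power.

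**Working it through.** **1. How the loss arises.**
- Loss to follow-up: a team decision after randomisation can end participation in the trial.
- Follow-up sections: a hernia can be found at any of three scans, and the 2-year scan closes the endpoint.
- Statistical methods: an outcome that is missing leaves the primary analysis.

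Taken together, a discretionary decision after randomisation can affect who contributes to the primary comparison. The non-compliance ground also reaches people who remain contactable, since those who are not contactable have their own ground.

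**2. The plan's own sample size.** Inputs from Sample size and Statistical methods: 25% v 10%, two-sided 5%, power 80%, 20% loss. With pooled variance and no continuity correction,

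n per arm = [1.960 × √(2 × 0.175 × 0.825) + 0.842 × √(0.25 × 0.75 + 0.10 × 0.90)]² / 0.15²
= (1.0532 + 0.4434)² / 0.0225 ≈ 99.5, rounded up to 100.

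The total is 200, and 200 / 0.80 = 250. The stated figures reproduce exactly.

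**3. Power if withdrawals add to the planned loss.** Power = Φ[(0.15√n − 1.0532) / 0.5268], with n = 125 × (1 − total loss). Losses above 20% are assumptions; the article gives no withdrawal rate.

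| Total loss | n per arm | Power |
|---|---|---|
| 20% (planned) | 100 | 80.2% |
| 22% | 97.5 | 79.2% |
| 25% | 93.75 | 77.6% |
| 30% | 87.5 | 74.7% |

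If the withdrawals fall within the planned 20%, the first row applies and power is unchanged.

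**4. Bias, for illustration only.** Suppose a share w of one arm is withdrawn and its hernia risk is m times the arm's average p. The observed risk is (p − w·m·p) / (1 − w). Both w and m are assumed.
- w = 5%, m = 2: 25% becomes (0.25 − 0.025) / 0.95 = 23.7%; 10% becomes (0.10 − 0.010) / 0.95 = 9.5%.
- w = 10%, m = 3: 25% becomes (0.25 − 0.075) / 0.90 = 19.4%; 10% becomes (0.10 − 0.030) / 0.90 = 7.8%.
- m = 1: no bias.

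**The case against.** The strongest case on the other side has five parts.

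- **Discarded results.** A reader might infer that withdrawal deletes a participant's outcome. The article does not say so. It omits missing values, not withdrawn people, and because the endpoint is cumulative, a hernia found at 3 months or 1 year could still count. The handling of collected data may be settled in the full protocol or the statistical analysis plan. This stands. The point is therefore about scans no longer sought, which an analysis plan cannot recover.
- **Contradiction of intention-to-treat.** A reader might infer an outright contradiction. Nobody is moved between arms, and Protocol deviations keeps the intention-to-treat analysis, removing major deviations only from the per-protocol set. This largely stands. What remains is avoidable missing data in a complete-case analysis that carries the intention-to-treat label.
- **Unblinded selection.** A reader might infer that unblinded staff could withdraw people selectively by arm. Integrity of data collection assigns outcome collection to blinded staff, and operating surgeons are kept out of it. The withdrawal clause does not name who decides, but no route to arm-selective withdrawal is shown.
- **Narrowness.** The clause is permissive, is framed by the participant's best interests and requires persistent non-compliance. Many persistent non-attenders would have missing outcomes anyway. That is true, but not of those who would return at 2 years, and a ground defined by harm to data collection fits poorly under best interests.
- **Existing safeguards.** The 20% allowance and the multiple imputation limit the risk. They do not remove it: the imputation is secondary, and chained equations as commonly applied assume data missing at random, which selective withdrawal may violate.

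**Conclusion.** The point holds in a limited form. The withdrawal rule is stated text, not an omission. It serves no treatment purpose in a one-off surgical comparison, and it can cost a primary outcome that was still obtainable. The intra-operative exclusion ground in the same list raises the same problem, because it too takes effect after randomisation.

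The size is uncertain. There is no loss of power beyond plan if these withdrawals sit within the 20% allowance. The fall to 77.6% or 74.7% depends on assumed total losses of 25% or 30%. The direction and amount of any bias are unknown, and the milder illustration above moves an arm's risk by 0.5 to 1.3 percentage points.

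A reader might construct a more dramatic case. The planned result of 25/100 v 10/100 gives p = 0.005, and restoring five withdrawn Duramesh participants who all had a hernia gives 25/100 v 15/105 and p = 0.053. That needs every one of the five to have a hernia that no earlier scan had found, with no counterpart among controls. Nothing in the document makes this likely, so it is a worst case and not an estimate.

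**What to change.** Amend the Loss to follow-up section as follows.

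- Delete persistent non-compliance as a ground on which the team may withdraw a participant from the trial.
- State that meeting an intra-operative exclusion criterion after randomisation does not end follow-up.
- State that every randomised participant is invited to each remaining scheduled scan, including the 2-year scan, unless they withdraw consent.
- State that all protocol ultrasound results already collected are kept and analysed in the allocated arm.

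Hospital records should not be added as a source for the primary outcome. The Primary outcome and Three-month follow-up sections define it by ultrasound, and records would bring in unstandardised ascertainment.

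The cost is a wording amendment and a few more appointment invitations within the existing schedule. Recruitment began in June 2025, so the first 2-year scans fall due around June 2027 and the change can still protect them.

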### Statistical methods

Results will be reported in accordance with the CONSORT guidelines for randomised controlled trials [21]. Analyses will be on an intention-to-treat (ITT) basis and will be conducted according to a pre-specified statistical analysis plan. The primary analyses will use data from all participants randomised who provided written informed consent, whose data is suitable (i.e. not missing). Any missing data will be reported, and data will be summarised as observed without imputation. Missing data values will be omitted from the primary analyses.

Continuous demographic variables such as age and BMI will be summated by the mean ± standard deviation if found to be normally distributed, and median with range or inter-quartile range otherwise. Categorical variables will be summarised by the number and percentage in each category.

To allow for differences in outcomes between participating surgeons, all analysis will be performed using generalised mixed (multilevel) models. Study group will be included as a fixed effect, with surgeon as a random effect. The primary outcome, the occurrence of trocar-site hernia over 2 years, will be analysed using a model assuming a binomial distribution with an identity link function. This will enable the percentage difference in outcome between groups to be calculated, which will be presented with a corresponding confidence interval. Secondary outcomes measured on a binary scale will be analysed using an equivalent approach to the primary outcome. Length of stay in hospital will be analysed using a linear mixed model. This outcome is expected to follow a positively skewed distribution and will thus be given a log transformation before analysis. All tests will be two-sided and a *p* value < 0.05 will be considered as statistically significant. Confidence intervals will be calculated at the 95% level.

A sensitivity analysis will be performed for the primary outcome. This will use multiple imputation for patients with missing outcome data. This will be performed using chained equations.

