### Subgroup/exploratory analysis

We aim to conduct exploratory analysis of the primary outcome to investigate treatment effects in different patient subgroups. Subgroups will be BMI ≥ 30 versus < 30, diabetes versus no diabetes and emergency/expedited versus elective. The different effects of the intervention in patient subgroups will be explored by including subgroup and the subgroup by study group interaction in the mixed model. Where a significant interaction is found, the effects of the intervention in each subgroup will be quantified. Furthermore, patients in the control group will be analysed according to those who were closed with J-vicryl versus J-PDS.

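### The randomisation strata (BMI and diabetes) are left out of the stated analysis model, which forgoes a little precision and makes the test mildly conservative

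*Protocol article*

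**What the plan says.** Protocol article, Randomisation: "the computer-generated randomisation sequence (in 1:1 ratio) will use a block size of 4 and stratify according to BMI" at a cut-point of 30, and also according to diabetes. This gives four strata.

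Protocol article, Statistical methods: "all analysis will be performed using generalised mixed (multilevel) models". The terms are then named: "Study group will be included as a fixed effect, with surgeon as a random effect". The primary outcome "will be analysed using a model assuming a binomial distribution with an identity link function", so the treatment effect is a risk difference. Binary secondary outcomes follow the same approach, and length of stay has a linear mixed model on the log scale. Participants with missing outcomes are left out of the primary analysis.

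Protocol article, Subgroup/exploratory analysis: this is the only place where BMI and diabetes enter a model. Subgroup effects "will be explored by including subgroup and the subgroup by study group interaction in the mixed model". Those models are exploratory and do not supply the primary estimate.

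**The concern.** Balancing the arms within strata removes from the treatment comparison the part of the outcome variance that the strata explain. A model without the strata still counts that part in its standard error. If BMI and diabetes predict hernia, the confidence interval is therefore somewhat too wide and the test rejects slightly less often than 5% under the null.

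The choice of terms is also uneven. Surgeon, which did not constrain allocation, is in the model, while the two factors that did are not. What is at stake is precision that could be had at almost no cost. If the factors are not prognostic, nothing is lost.

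**Working it through.** **1. The plan's own sample size.** The inputs come from the Sample size section (25% versus 10%, 5% significance, 80% power, 20% loss). Two-sided testing comes from Statistical methods. With the pooled-variance formula, and mean risk (0.25 + 0.10)/2 = 0.175:

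n per arm = [1.96·√(2·0.175·0.825) + 0.8416·√(0.25·0.75 + 0.10·0.90)]² / 0.15² = [1.0532 + 0.4434]² / 0.0225 = 99.5, so 100.

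Power at 100 per arm is 80.2%, and 200/0.80 = 250. The stated figures reproduce. This calculation ignores the strata, so it does not depend on adjusting for them.

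**2. Direction and size with complete follow-up.** Assumptions not in the documents: 40% with BMI 30 or more; diabetes in 8% of those below 30 and 20% of those at 30 or above; no surgeon variance.

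The standard error without strata is √[(0.1875 + 0.0900)/100] = 0.0527, whatever the prognostic strength.

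Worked case, risk ratios of 2 for BMI and 2 for diabetes:
- The stratum weights are 0.552, 0.048, 0.320 and 0.080, with relative risks 1, 2, 2 and 4 (weighted mean 1.608).
- The stratum risks are 0.16, 0.31, 0.31 and 0.62 in the control arm, and 0.06, 0.12, 0.12 and 0.25 in the intervention arm.
- The true variance is the mean within-stratum variance, 0.2574/100, plus the variance of the stratum risk differences, 0.0063/200. The sum is 0.002605, so the SE is 0.0510.
- The unadjusted SE is too large by 0.0527/0.0510 − 1 = 3.2%.
- Unadjusted power is Φ[(0.15 − 1.96·0.0527)/0.0510] = 82.0%. Adjusted power is Φ[0.15/0.0510 − 1.96] = 83.6%.
- Under the null (17.5% in both arms) the actual type I error is about 0.043.

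Other strengths by the same formulas:

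| Risk ratios (BMI, diabetes) | SE too large by | Type I error, unadjusted | Power, unadjusted to adjusted |
|---|---|---|---|
| 1, 1 | 0% | 0.050 | 81.3% to 81.3% |
| 1.5, 1.5 | 0.9% | 0.048 | 81.5% to 82.0% |
| 2, 2 | 3.2% | 0.043 | 82.0% to 83.6% |
| 3, 2 | 5.9% | 0.038 | 82.6% to 85.4% |

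**3. With the planned 20% loss.** The table assumes that balance survives to analysis, but the plan balances 250 and analyses about 200. In a stratum of N split evenly, random 20% loss gives the difference in arm sizes a variance of 2·(N/2)·0.8·0.2 = 0.16N. Simple randomisation of the same 0.8N would give 0.8N. So about one fifth of the chance imbalance returns, and the miscalibration shrinks.

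This was simulated with 250 randomised in stratified blocks of 4, 20% random loss, 40% with BMI 30 or more, 12% diabetic and no surgeon effect. Strength is expressed as odds ratios for BMI and diabetes:
- 2 and 1.5: power gain about 0.4 points, with type I error close to 5%.
- 3 and 2: power gain about 1.3 points.
- 4 and 2.5: power gain about 2 points.

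At the two stronger settings the unadjusted null rejection rate was 4.3% to 4.7% over 6,000 runs per scenario. The simulation error is about 1.96·√(0.05·0.95/6000) = 0.6 points, so these rates are only roughly distinguishable from 5%.

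**The case against.** **The effect is small and rests on assumptions.** This stands. No section gives the prevalence or prognostic strength of either factor, and the Eligibility criteria exclude BMI of 40 or more, which removes the most extreme contrast. With weak predictors the two analyses can hardly be told apart.

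**A reader might infer that part of the stated 80% power is lost.** The documents do not support that. The sample size calculation ignores the strata and reproduces at 80.2%, and unadjusted power stays above 80% in every case computed. What is forgone is a margin above the planned power.

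**A reader might infer a clearly miscalibrated test.** With complete follow-up and odds ratios of 4 and 2.5, simulated type I error is about 3.9% to 4.1%. That leaves out the loss the trial itself plans for, under which the rate moves closer to 5%.

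**A reader might infer that chance imbalance among those analysed invalidates the result.** It does not. The unadjusted standard error already allows for chance imbalance. Adjustment improves precision and does not rescue validity.

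**The analysis plan, not shown, may list the strata.** It may. But the article does not leave the model open: it names the distribution, link, fixed effect and random effect. If the analysis plan adds terms, the two texts need to be aligned.

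**Extra terms may break the model.** This also stands. A binomial identity-link mixed model with a 10% arm can fail to converge or give fitted risks outside 0 to 1. The gains above come from simpler adjusted estimators without a surgeon effect, not from that model, so a fallback is part of the fix.

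**Conclusion.** The point holds as a small efficiency recommendation. The protocol stratifies on two factors and states a model that omits both. If the factors are prognostic, the standard error is slightly too large, the test mildly conservative and a little precision is given up. Under assumed odds ratios from 2 and 1.5 to 4 and 2.5, with 40% at BMI 30 or more, 12% diabetic and 20% random loss, the gain is about 0.4 to 2 points of power and the unadjusted type I error about 4.3% to 5%. If the factors are not prognostic, the gain is nil.

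The omission does not bias the estimate or inflate type I error. The 80% power and the 250 participants are unaffected. The mismatch in the text is certain; the size of its consequence is not.

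**What to change.** In Statistical methods, and in the analysis plan to match:
- Add BMI stratum and diabetes stratum, as used at randomisation, as fixed effects in the primary model and in each secondary model with enough events to support them. The log length-of-stay model can take them directly.
- Keep the marginal risk difference with its 95% confidence interval as the reported effect.
- Pre-specify a fallback for non-convergence, for example standardisation from a logistic model or a stratified Mantel-Haenszel risk difference, and say how surgeon is handled in it.

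No new data are needed, because both factors must be known to randomise each participant. The cost is a few sentences, a modest convergence risk and the extra fallback step. Recruitment is expected to run to December 2026 and the outcome is measured over two years, so the change can be made well before the final outcome data are complete.
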